### Secondary outcomes

These include:Incidence of periumbilical surgical site infection (SSI) within 90 days, categorised by the Centers for Disease Control and Prevention (CDC) [14] as superficial, deep and organ-space.Incidence of periumbilical surgical site occurrence (SSO) within 90 days, categorised by the Ventral Hernia Working Group (VHWG) [15] as SSI, seroma, haematoma, superficial dehiscence, fascial dehiscence, enterocutaneous fistula, suture granuloma and chronic sinus tract.Reoperation within 90 days of the index operation.Length of hospital stay.Mortality within 90 days of the index operation.Measurement of postoperative quality of life (QoL) using modified versions of validated questionnaires – EuraHS-QoL score [16] and Carolinas Comfort Scale (CCS) [17, 18].

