### Statistical methods

Results will be reported in accordance with the CONSORT guidelines for randomised controlled trials [21]. Analyses will be on an intention-to-treat (ITT) basis and will be conducted according to a pre-specified statistical analysis plan. The primary analyses will use data from all participants randomised who provided written informed consent, whose data is suitable (i.e. not missing). Any missing data will be reported, and data will be summarised as observed without imputation. Missing data values will be omitted from the primary analyses.

Continuous demographic variables such as age and BMI will be summated by the mean ± standard deviation if found to be normally distributed, and median with range or inter-quartile range otherwise. Categorical variables will be summarised by the number and percentage in each category.

To allow for differences in outcomes between participating surgeons, all analysis will be performed using generalised mixed (multilevel) models. Study group will be included as a fixed effect, with surgeon as a random effect. The primary outcome, the occurrence of trocar-site hernia over 2 years, will be analysed using a model assuming a binomial distribution with an identity link function. This will enable the percentage difference in outcome between groups to be calculated, which will be presented with a corresponding confidence interval. Secondary outcomes measured on a binary scale will be analysed using an equivalent approach to the primary outcome. Length of stay in hospital will be analysed using a linear mixed model. This outcome is expected to follow a positively skewed distribution and will thus be given a log transformation before analysis. All tests will be two-sided and a *p* value < 0.05 will be considered as statistically significant. Confidence intervals will be calculated at the 95% level.

A sensitivity analysis will be performed for the primary outcome. This will use multiple imputation for patients with missing outcome data. This will be performed using chained equations.

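### One identity-link binomial mixed model is prescribed for every binary outcome; for very rare outcomes such as 90-day mortality it will often give no valid interval, and for the primary outcome it carries a boundary risk.

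*Protocol article*

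**What the plan says.** In the protocol article, Statistical methods requires that "all analysis will be performed using generalised mixed (multilevel) models". The terms are given as "Study group will be included as a fixed effect, with surgeon as a random effect". The primary outcome, trocar-site hernia over two years, "will be analysed using a model assuming a binomial distribution with an identity link function". The reason given is the scale of the result: "This will enable the percentage difference in outcome between groups to be calculated, which will be presented with a corresponding confidence interval".

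The same section then carries the model over: "Secondary outcomes measured on a binary scale will be analysed using an equivalent approach to the primary outcome". Under Secondary outcomes the binary items are surgical site infection (SSI), surgical site occurrence (SSO) and reoperation, all within 90 days, and "Mortality within 90 days of the index operation". No expected rate is given for any of these four. Adverse event reporting cites 0% for suture granuloma and 0.3% for chronic sinus with Duramesh, and says that both are reported as secondary outcomes.

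The article names no alternative for an arm without events or for a fit that does not converge. It does say that the analyses "will be conducted according to a pre-specified statistical analysis plan", and that plan is not available here.

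**The concern.** Two features of the prescribed model need to be kept apart.

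The first concerns sparse data. On the identity scale the group coefficient is the difference between two proportions. If an arm has no events, its fitted risk is zero, on the edge of the parameter space, and the usual standard error contributes nothing for that arm. If neither arm has events, the interval collapses to a point at zero. A reader would then see either no interval for mortality or one that is far too narrow.

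The second concerns the surgeon effect. A normally distributed intercept added on the probability scale is unbounded. Where the mean risk is low and surgeons vary, part of that distribution lies below zero, where the binomial likelihood is not defined. Software may then stop, truncate, or push the surgeon variance towards zero.

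At stake are usable intervals for the rarest outcomes and a primary model whose behaviour depends on a surgeon variance that is unknown at present.

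**Working it through.** **Inputs from the protocol article.** Control risk 25%, Duramesh risk 10%, two-sided 5%, power 80%, 20% loss, 250 randomised 1:1, so 125 per arm (Sample size; Statistical methods; Abstract). Twelve surgeons: ten consultants and two associate specialists (Setting). Chronic sinus 0.3% (Adverse event reporting).

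**Inputs assumed, because the article gives none.** Mortality of 0.5% to 1%; equal risk in both arms for the sparse-event calculation; a normal surgeon effect with a between-surgeon SD of 3 to 10 percentage points.

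**1. The article's own figure.** With pooled variance and no continuity correction,

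n = [1.96·√(2·0.175·0.825) + 0.8416·√(0.25·0.75 + 0.10·0.90)]² / 0.15² = (1.0532 + 0.4434)² / 0.0225 = 99.5,

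which rounds up to 100 per group; 200/0.8 = 250. The stated size reproduces, and this point does not affect it.

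**2. Chance of an empty arm.** For risk p and 125 per arm, the chance of no events in one arm is a = (1 − p)^125. In at least one arm it is 1 − (1 − a)², and in both it is a².

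| Risk | One given arm | At least one arm | Both arms |
|---|---|---|---|
| 0.3% | 0.687 | 90% | 47% |
| 0.5% | 0.534 | 78% | 29% |
| 1% | 0.285 | 49% | 8% |
| 2% | 0.080 | 15% | 0.6% |
| 3% | 0.022 | 4% | <0.1% |
| 5% | 0.002 | 0.3% | <0.1% |

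The problem is concentrated at risks of about 1% and below.

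**3. What the interval looks like.** Simple risk differences with 125 per arm, ignoring surgeon:

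| Events | Wald 95% interval (points) | Newcombe 95% interval (points) |
|---|---|---|
| 0 v 0 | 0 to 0 | −3.0 to +3.0 |
| 1 v 0 | −0.8 to +2.4 | −2.3 to +4.4 |

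For 1 v 0 the Wald standard error is √(0.008·0.992/125) = 0.80 points, and it comes wholly from the arm with the event.

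**4. Surgeon effect in the primary model.** For mean risk p and surgeon SD s, the implied chance that one surgeon's probability is negative is Φ(−p/s). For at least one of 12 it is 1 − (1 − Φ(−p/s))^12.

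| SD (points) | 10% arm | 25% arm |
|---|---|---|
| 3 | 0.5% | <0.1% |
| 5 | 24% | <0.1% |
| 7 | 62% | 0.2% |
| 10 | 87% | 7% |

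At SD 5: Φ(−2) = 0.0228 and 1 − 0.9772^12 = 0.241. These figures show how far the assumed distribution spills outside 0–1. They are not rates of failed fits.

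A small simulation points the same way (25% v 10%, 200 patients, 12 surgeons, 100 runs per setting). With logit-scale surgeon SDs of 0.3, 0.5 and 0.8, the fitted lower-arm mean minus two fitted SDs was below zero in 33%, 50% and 71% of fits. That too measures closeness to the boundary, not non-convergence.

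**5. If the surgeon variance is estimated as zero.** Study group is then the only term and the model returns the observed difference. At exactly 25/100 v 10/100 the standard error is √(0.2775/100) = 5.27 points, giving 15 ± 10.3, or 4.7 to 25.3 points. That is a usable result.

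**The case against.** The strongest reply is that the identity link is a recognised route to a risk difference. At 25% versus 10% both risks are well away from zero, and a zero surgeon variance does no harm (step 5). All of this stands. A reader might infer that the primary analysis will fail or is invalid, but the documents do not support that: they give no surgeon variance, and the result in step 4 runs from 0.5% to 87% across the assumed range.

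A reader might also infer that the model can give no interval for any uncommon outcome. That is strictly so only when an arm has no events. With a few events in each arm an interval may be obtained, though its coverage may be poor. Nor is the problem shown for SSI or SSO: no overall rate is given for either, and SSO is a composite with eight categories.

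The subgroup interactions add little. They are exploratory, apply to the primary outcome only, and with one binary subgroup the fixed part of the model is still saturated.

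A further tempting inference is that a replacement model would be picked after unblinding. That presumes that the analysis plan has no fallback. Such rules are ordinary content for that plan, so their absence from a journal article is not an error.

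Finally, Publication policy says that safety data are reported descriptively, so deaths would be counted by arm in any case. That softens the consequence. But mortality is a listed binary secondary outcome, so the modelling rule as written still covers it. The objection does not remove the fact that the article positively prescribes this model for outcomes it cannot be expected to handle.

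**Conclusion.** The point holds in limited form. For very rare binary outcomes the prescribed rule is badly fixed: at assumed mortality of 0.5% to 1% there is a 78% to 49% chance that at least one arm is empty and the usual interval is not valid. At the cited chronic sinus rate of 0.3%, applied to both arms and taken as a separate outcome, the chance is 90%. The article does not say whether granuloma and sinus will be modelled separately from SSO, so mortality is the clearer example.

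For the primary outcome the model is legitimate, with a boundary and convergence risk that is negligible if surgeons differ by about 3 points (SD) and material from about 5 points upwards. This rests on a normal surgeon effect and on SDs that the documents do not supply. The matter should be corrected, but it does not threaten the design.

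**What to change.** Keep the risk difference in percentage points as the estimand, and change how it is obtained.

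- **Sparse outcomes** (no events in an arm, or very few in total): replace the identity-link mixed model with the unadjusted risk difference, a Newcombe score interval and an exact test. The threshold for very few should be fixed as a number in advance; fewer than 10 events in total is one possible choice, not derived here. A separate rule is needed because a logistic model also breaks down when an arm is empty.
- **Primary and more common binary outcomes:** obtain the risk difference by marginal standardisation from a logistic mixed model with study group, BMI group, diabetes and random surgeon, with a delta-method or bootstrap interval. BMI and diabetes are the stratification factors named under Randomisation, but Statistical methods does not list them among the model terms. Alternatively, keep the identity-link model and name this one as the fallback if it does not converge.

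If the analysis plan already contains such rules, the article's wording need only be aligned with it. The cost is a short change of wording, slightly more analysis work, and a different method for the rarest outcomes. Sample size and data collection do not change. Recruitment is expected to run to December 2026 with two years of follow-up after that, so there is time to settle it before analysis.

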### Sample size

This study will be powered for detecting a difference in the primary outcome between groups. Previous prospective studies with similar follow-up duration record an incidence of trocar-site hernia in the region of 25% [7–9]. An absolute reduction in primary outcome of 15% is expected within the intervention group, down to an occurrence of 10%. The best available evidence comes from a systematic review of Duramesh implantation for laparotomy and ventral hernia repair with a median incisional hernia rate of 3.4% after 1 year [13]. An occurrence of 10% was selected as a conservative estimate of the effect size in the intervention group after 2 years. Therefore, using a significance level of 5% and power of 80%, it is calculated that 100 patients per group, 200 in total, are required. After factoring in a 20% rate of loss to follow-up, a total of 250 participants will be included in the trial.

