### Subgroup/exploratory analysis

We aim to conduct exploratory analysis of the primary outcome to investigate treatment effects in different patient subgroups. Subgroups will be BMI ≥ 30 versus < 30, diabetes versus no diabetes and emergency/expedited versus elective. The different effects of the intervention in patient subgroups will be explored by including subgroup and the subgroup by study group interaction in the mixed model. Where a significant interaction is found, the effects of the intervention in each subgroup will be quantified. Furthermore, patients in the control group will be analysed according to those who were closed with J-vicryl versus J-PDS.

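### The length-of-stay model leaves out urgency of surgery, a likely strong predictor known before randomisation; the comparison stays valid but loses precision

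*Protocol article*

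**What the plan says.** The Statistical methods section of the protocol article sets one structure for all analyses: "Study group will be included as a fixed effect, with surgeon as a random effect". For the outcome at issue, "Length of stay in hospital will be analysed using a linear mixed model", with a log transformation because the distribution is expected to be skewed. Binary secondary outcomes, which include surgical site infection (SSI) and surgical site occurrence (SSO), follow the primary outcome's binomial identity-link model. No baseline covariate is named for any of these.

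Three other sections bear on the point:
- Eligibility criteria admits both elective and emergency operations.
- Randomisation stratifies by BMI and diabetes only.
- Subgroup/exploratory analysis lists, among the subgroups for the primary outcome, "diabetes versus no diabetes and emergency/expedited versus elective", each entered in the mixed model with its interaction with study group.

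**The concern.** Urgency is settled before the patient is randomised in the anaesthetic room, so it is a true baseline variable. The planned subgroup analysis cannot be run without it, so the investigators must intend to hold it and are prepared to model it. Yet it enters only the exploratory analysis of the hernia outcome, and not the analysis of length of stay, where it is likely to matter most. Stratification does not balance it. The surgeon effect, included to allow for differences between surgeons, replaces it only so far as surgeons differ in their mix of urgent and elective work.

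The difference in stay between urgent and elective patients therefore remains in the residual variance. What is at stake is the width of the confidence interval for the ratio of stays between arms.

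**Working it through.** **The plan's own figure.** The only sample size stated is for the primary outcome: "using a significance level of 5% and power of 80%, it is calculated that 100 patients per group, 200 in total, are required". With 25% v 10%, two-sided 5% and 80% power (pooled variance, no continuity correction):

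n = (1.96 × √(2 × 0.175 × 0.825) + 0.8416 × √(0.25 × 0.75 + 0.10 × 0.90))² / 0.15² = (1.053 + 0.443)² / 0.0225 ≈ 99.5, so 100 per group.

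Then 200 / 0.8 = 250. The stated figures reproduce. No power or precision is stated for length of stay.

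**Inputs for length of stay.** From the article: 250 patients at 1:1, so 125 per arm. Assumed, because the documents give none:
- share of urgent (emergency/expedited) cases, p = 0.3 to 0.5
- within-group SD of log stay, s = 0.7 to 0.9
- ratio of urgent to elective stay, r = 1.5, 2 or 3, with b = ln r

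**Formulas.** Variance explained by urgency: R² = p(1−p)b² / (p(1−p)b² + s²). Unadjusted over adjusted standard error: 1/√(1−R²) = √(1 + p(1−p)b²/s²). Equivalent increase in patients: p(1−p)b²/s².

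Example, r = 2: b² = 0.480.
- Low end (p = 0.3, s = 0.9): 0.21 × 0.480 = 0.101; R² = 0.101/0.911 = 11%; SE ratio √(1 + 0.101/0.81) = 1.06.
- High end (p = 0.5, s = 0.7): 0.25 × 0.480 = 0.120; R² = 0.120/0.610 = 20%; SE ratio √(1 + 0.120/0.49) = 1.12.

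| Urgent stay relative to elective | Variance explained | Standard error too large by | Equivalent extra patients |
|---|---|---|---|
| 1.5 times | 4-8% | 2-4% | 4-8% |
| 2 times | 11-20% | 6-12% | 12-25% |
| 3 times | 24-38% | 15-27% | 31-62% |

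**Effect on the interval.** Take r = 3, s = 0.8, p = 0.5. Unadjusted SE = √((0.64 + 0.302) × 2/125) = 0.123; adjusted SE = √(0.64 × 2/125) = 0.101. The 95% limits on the ratio of geometric mean stays go from a factor of exp(1.96 × 0.123) = 1.27 either way to exp(1.96 × 0.101) = 1.22.

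**Validity.** A null simulation of this case (20,000 trials, 125 per arm, simple linear model without the surgeon effect) gave a mean log difference of 0.0005 without urgency and 0.0006 with it, and type I error of 4.9% and 4.8%. The empirical SD of the estimate was 0.122 and 0.101. Only precision differs.

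**Wound outcomes.** Assuming event rates of 3-10% in elective and 6-20% in urgent patients, adjustment cuts the standard error by only 0.3-2.8%. A 10-point imbalance in urgency between arms would move the risk difference by 0.3-1.5 points, against a standard error of 2.5-4.5 points.

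**The case against.** An unadjusted randomised comparison is valid, so nothing here is wrong in the strict sense. Length of stay is one of several secondary outcomes and carries no power claim. The article refers to a pre-specified statistical analysis plan that is not shown and may add covariates. Every input to the size is assumed, and at the low end the gain is only 2%. The article does not give each surgeon's mix of urgent and elective work; where mixes differ, the surgeon effect already absorbs part of the urgency variance, and the tabled figures are upper bounds.

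Most of this stands and limits the point to efficiency. It does not remove it: the article names the model terms for all analyses, so the comment is on a stated method rather than on a missing detail.

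A reader might infer three stronger things, which the documents do not support:
- **That chance imbalance in urgency biases the result.** Imbalance will occur: with 30-50% urgent cases, a gap above 10 points between arms arises in about 8-11% of trials, and at a threefold ratio it would shift the ratio of stays by a factor of 3^0.1 = 1.12. But it averages to zero over randomisations and the unadjusted interval already allows for it. Counting it as a harm on top of the wider interval would largely count the same variance twice.
- **That SSI and SSO suffer in the same way.** The gain there is at most about 3% of the standard error, and extra terms in an identity-link mixed model with few events can hinder convergence.
- **That urgency is documented as a recorded item.** The data listed under Participant timeline and baseline data do not name it. That it will be captured is inferred from the planned subgroup analysis.

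**Conclusion.** The point holds for length of stay only, as an avoidable loss of precision. With 30-50% urgent cases and a within-group SD of log stay of 0.7-0.9, the standard error is about 2-4% too large if urgent stays are 1.5 times as long, 6-12% if twice and 15-27% if three times, less whatever the surgeon effect takes up. Whether this is material depends on a ratio of stays that the documents do not give. It is a nearly free improvement to an unpowered secondary analysis, not an error. The primary analysis and the total of 250 are untouched.

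**What to change.** Before unblinding, pre-specify urgency (emergency/expedited v elective, the grouping already used for the subgroup analysis) as a fixed effect in the log length-of-stay mixed model, keeping study group and the surgeon random effect. Report the model without urgency as a supporting analysis. Confirm that the eCRF captures urgency for every patient. If the statistical analysis plan already includes the term, nothing further is needed.

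Keep the stated models for SSI and SSO; any adjustment for urgency there should be at most an optional sensitivity analysis.

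The cost is one extra parameter and a sentence of model description. Fixing the term in advance also avoids any suggestion that adjustment was chosen after seeing the results.

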### Subgroup/exploratory analysis

We aim to conduct exploratory analysis of the primary outcome to investigate treatment effects in different patient subgroups. Subgroups will be BMI ≥ 30 versus < 30, diabetes versus no diabetes and emergency/expedited versus elective. The different effects of the intervention in patient subgroups will be explored by including subgroup and the subgroup by study group interaction in the mixed model. Where a significant interaction is found, the effects of the intervention in each subgroup will be quantified. Furthermore, patients in the control group will be analysed according to those who were closed with J-vicryl versus J-PDS.

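### The plan provides for quantifying subgroup effects only where the interaction is significant, a filter that a trial of this size would seldom pass

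*Protocol article*

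**What the plan says.** The Subgroup/exploratory analysis section states its aim: "We aim to conduct exploratory analysis of the primary outcome to investigate treatment effects in different patient subgroups". There are three factors: BMI at or above 30 versus below, "diabetes versus no diabetes and emergency/expedited versus elective". The method is "including subgroup and the subgroup by study group interaction in the mixed model". The reporting rule follows: "Where a significant interaction is found, the effects of the intervention in each subgroup will be quantified". Nothing is said about subgroup-level estimates when the interaction is not significant.

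Statistical methods sets the threshold: "All tests will be two-sided", with p below 0.05 counted as significant. It also fixes the scale, a binomial model with identity link, so effects are risk differences.

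The Sample size section addresses only the overall comparison of 25% with 10%, for which "100 patients per group, 200 in total, are required". The article gives no subgroup proportions, expected interaction or interaction power.

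**The concern.** The rule makes presentation of an estimate depend on its p value, in a trial that was not sized for that test. Two things follow.

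- **Real differences in effect would usually leave no subgroup estimates.** A reader who sees none may conclude that the effect is alike in obese and non-obese patients, or in emergency and elective patients, when the data could not exclude a large difference.
- **The estimates that do appear have passed a significance filter.** On average they exaggerate the difference between subgroups.

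This matters here because BMI and diabetes are the randomisation strata, and because the Abstract and Discussion both present the trial as informing emergency and elective practice. Calling the analysis exploratory limits the claims that can be made from it, but does not undo selection on significance.

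**Working it through.** **Inputs from the protocol article.** Control risk 25%, Duramesh risk 10%, two-sided 5% level, 80% power, 100 evaluable per arm, 20% loss (Sample size; Statistical methods). 1:1 allocation (Randomisation). Risk-difference scale (Statistical methods).

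**Assumptions, because the article gives no figures.** Subgroup splits from 50/50 to 10/90. Control risk 25% in both levels. True interaction of 15 points, taken either as reductions of 22.5 and 7.5 points or as 15 and 0, with the larger reduction in the smaller level. Surgeon effect ignored.

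**Step 1: reproduce the planned size.**

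n per arm = [1.96·√(2·0.175·0.825) + 0.8416·√(0.25·0.75 + 0.10·0.90)]² / 0.15² = (1.0532 + 0.4433)² / 0.0225 = 99.5, so 100.

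Allowing for loss: 200 / 0.8 = 250. Power at 100 per arm is 80.2%. The stated design reproduces.

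**Step 2: standard error of the interaction.** The interaction is the difference between two risk differences, so SE = √Σ p(1−p)/n over four cells.

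For 50/50 with reductions of 22.5 and 7.5, each cell has 50 patients and risks of 25%, 2.5%, 25% and 17.5%:

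SE = √(0.00375 + 0.00049 + 0.00375 + 0.00289) = 0.1043.

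The SE of the main effect is √(0.2775/100) = 0.0527, about half of this.

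**Step 3: power and exaggeration.** Power = Φ(0.15/SE − 1.96) + Φ(−0.15/SE − 1.96). In the example, 0.15/0.1043 = 1.438, which gives 30.1%. Exaggeration is the mean absolute estimate given p<0.05, divided by 0.15, from 1,000,000 normal draws per row.

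| Split | Reductions (points) | SE | Power | Exaggeration |
|---|---|---|---|---|
| 50/50 | 22.5 v 7.5 | 0.1043 | 30.1% | 1.80 |
| 30/70 | 22.5 v 7.5 | 0.1086 | 28.2% | 1.87 |
| 20/80 | 22.5 v 7.5 | 0.1214 | 23.5% | 2.06 |
| 10/90 | 22.5 v 7.5 | 0.1577 | 15.8% | 2.61 |
| 50/50 | 15 v 0 | 0.1142 | 25.9% | 1.95 |
| 30/70 | 15 v 0 | 0.1209 | 23.7% | 2.05 |
| 20/80 | 15 v 0 | 0.1362 | 19.6% | 2.28 |
| 10/90 | 15 v 0 | 0.1787 | 13.4% | 2.93 |

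The smallest estimate that can reach significance is 1.96·SE: about 20 to 22 points at 50/50 and 31 to 35 points at 10/90. Each exceeds the 15-point main effect.

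**Step 4: binomial check.** In 300,000 simulated trials at 50/50 with true reductions of 22.5 and 7.5, power was 30.5%. Among the significant trials, the subgroup reductions averaged 27.0 and 0.1 points. At 10/90 the simulated powers were 15.1% and 15.8% for the two patterns. The normal approximation is rough with 10 patients per cell, but the picture is the same.

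**Step 5: other sizes of interaction.**

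- **10 points (20 v 10):** power 15.9% at 50/50 down to 9.3% at 10/90; exaggeration 2.6 to 4.0 times.
- **20 points, with the planned 25% and 10% variances in every cell:** power 47.5% down to 20.6%.
- **80% power:** needs (1.96 + 0.8416)·SE, which is 2.8016 × 0.1054 = 29.5 points at 50/50 and 2.8016 × 0.1756 = 49.2 points at 10/90.
- **No true interaction:** at least one of three tests is significant with probability 1 − 0.95³ = 14.3% if they are independent. At 50/50 the spurious difference then quantified averages about 24 points.

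**Sensitivity to control risk.** With control risks of 35% and 20% in the two levels and reductions of 22.5 and 7.5, power is 27.5% (exaggeration 1.89) at 50/50 and 12.3% (3.13) at 10/90, slightly beyond the range in the table.

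**The case against.** The approach has merits. The subgroups are few, named in advance, labelled exploratory and tested by interaction rather than by separate p values within strata. Asking for evidence of interaction before showing stratum effects can be defended as a guard against over-reading noisy strata. The layout of tables and forest plots commonly belongs in the analysis plan, which is not shown. These points lower the severity. They do not remove the defect, because the protocol states a rule here rather than leaving a gap, and an analysis plan that follows the sentence inherits it.

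It is also fair that, when an interaction is significant, the same estimate is printed with or without the change. What is gained is a complete set of estimates with intervals, not a different number in that case.

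A reader might infer three stronger things that the document does not support:

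- **That interactions themselves go unreported.** The interaction model is to be fitted for all three factors, and nothing says that its estimate, interval or p value will be withheld. The condition covers only the effects within subgroups.
- **That any effect quantified must overstate the truth.** Exaggeration after a significance filter is an average property, and it shrinks as the true interaction grows.
- **That the data would be lost for pooling with the other periumbilical trocar-site trial described in the Discussion.** Data sharing and Data Availability commit to a public anonymised dataset, with participant-level data available on request.

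**Conclusion.** The point holds as a moderate reporting defect. Under the stated rule, the subgroup effects would be quantified in roughly 13% to 31% of trials if the true interaction were 15 points, and the interaction estimates that passed would average about 1.8 to 2.9 times the truth. For interactions up to about 20 points, power is below 50% at every split considered. With an even split, the filter would open more often than not only above about 21 points.

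These figures rest on 100 evaluable patients per arm, the assumed splits, a 25% control risk in both levels and no surgeon effect. The article supplies only the first of these and the overall 25%. The primary estimate, its test, the sample size and the main conclusion are untouched.

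**What to change.** Replace the conditional sentence in Subgroup/exploratory analysis with:

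> For all three pre-specified subgroups, the risk difference with 95% CI in each level and the interaction estimate with 95% CI and p value will be reported irrespective of significance, and labelled exploratory.

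This removes selection on significance from the reported set. It costs one sentence and, at most, one forest plot, with no added patients or data collection. Recruitment is expected to run to December 2026 and follow-up lasts two years, so the change can be made before the 2-year results are complete.
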